## Abstract

**Background:**

Ankle instability limits physical activities and undermines a person’s quality of life. Tai Chi’s health benefits have been reported in different population groups. However, the effects of Tai Chi on neuromuscular function among young adults with functional ankle instability (FAI) remain unclear. Therefore, we aim to investigate the effect of Tai Chi on young adults with FAI.

**Methods:**

This study will be conducted as a randomized controlled trial with blinded assessors. A total of 104 young adults with FAI will be recruited and randomly assigned to intervention and control groups. The participants in the simplified Tai Chi exercise program (STCEP) group will receive a 12-week Tai Chi training. The participants in the control group will receive a low-intensity exercise program and health education for 12 weeks. The primary and secondary outcomes will be assessed at baseline, 4th, 8th, and 12th weeks. Primary outcome measures will include the Cumberland Ankle Instability Tool (CAIT) score, kinematics/kinetics data, electromyography during single-leg landing tasks, and the modified Star Excursion Balance Test (mSEBT). Secondary outcome measures will include the total time of Dynamic Leap and Balance Test (DLBT), ankle muscle strength, and ankle proprioception.

**Discussion:**

This study will investigate the effects of Tai Chi exercise on the neuromuscular function of patients with FAI, as indicated by ankle joint biomechanics, ankle proprioception, balance, ankle muscle strength, and ankle muscle activation. Results will demonstrate that Tai Chi can be an effective exercise for young adults with FAI.

**Trial registration:**

Chinese Clinical Trial Registry ChiCTR2100044089. Registered on 10 March 2021

## Administrative information

Note: the numbers in curly brackets in this protocol refer to SPIRIT checklist item numbers. The order of the items has been modified to group similar items (see http://www.equator-network.org/reporting-guidelines/spirit-2013-statement-defining-standard-protocol-items-for-clinical-trials/).

## Introduction

### Background and rationale {6a}

Acute ankle sprain is one of the most common musculoskeletal injuries in sports [1]. Approximately 40–75% of ankle sprains may lead to chronic ankle instability (CAI) [2]. Functional ankle instability (FAI) is the most common type of CAI. The symptoms of FAI include giving away or subjective ankle instability, sensorimotor impairments, and a high ankle sprain recurrence rate [3]. Individuals with FAI have a substantially higher risk of ankle abnormal biomechanics, which may lead to ankle osteoarthritis. This condition will adversely affect the daily living activities of patients with FAI [2].

Neuromuscular control at the ankle provides the unconscious activation of dynamic restraints that occur in preparation for and in response to ankle joint motion and loading [4]. Repeated ankle sprains may lead to neuromuscular deficits, which significantly impair the ankle stability [5]. Patients with FAI have deficits on joint position sense on the affected side compared with those of the healthy contralateral side [6]. Caulfield et al. collected the surface electromyography (sEMG) of peroneus longus of patients with FAI during landing tasks. They found that activation in the peroneus longus muscle reduces during the experimental period immediately prior to initial contact compared with that of the healthy control [7]. In addition, Delahunt et al. found that patients with FAI have a reduced dorsiflexion position and a decreased sagittal plane angular velocity during landing compared with those of the healthy control [8]. Therefore, the neuromuscular function of patients with FAI should be improved to prevent and treat ankle sprain injury.

Regular exercise training is essential for the rehabilitation of patients with FAI [9]. One of the traditional Chinese forms of exercise is Tai Chi, which has many characteristics that can help patients with FAI improve their neuromuscular control problems. Tai Chi is characterized by continuous slow movements with unilateral to bilateral shifts of body weight, a large range of motions at the joints, and smooth foot movement in various directions [10]. Slow, steady, and coordinated movements likely improve joint proprioception; they also activate and strengthen deep ankle muscles [11]. Therefore, the primary emphasis on posture control may make Tai Chi a relevant and appropriate alternative exercise for neuromuscular deficits among patients with FAI. Recently, one study has applied Tai Chi to treat FAI. A study has shown that 12-week traditional 24-form Tai Chi training can improve the Cumberland Ankle Instability Tool (CAIT) score and the modified Star Excursion Balance Test (mSEBT) performance [12]. However, they are insufficient to prove that Tai Chi is effective for patients with FAI. The effects of Tai Chi exercise on neuromuscular function, joint biomechanics, and physical functioning in individuals with FAI should be further investigated to understand the clinical effects and relevant mechanism of the treatment.

In this study, a simplified Tai Chi exercise program (STCEP) specifically for patients with FAI will be developed. A randomized controlled trial will be conducted to investigate the clinical efficacy of 12-week STCEP on neuromuscular function. The results of the present study will determine the effectiveness and provide scientific evidence to establish a form of comprehensive sports rehabilitation for patients with FAI.

### Trial design {8}

The effectiveness of STCEP on young adults with FAI will be studied using a randomized, single-blind, and parallel-controlled trial. Eligible participants will be randomized at a 1:1 ratio and enrolled in one of the two groups with allocation concealment and assessor blinding. The study will be carried out over a 12-week intervention (i.e., a simplified Tai Chi exercise program). An overview of the study is displayed in Fig. 1.

**Fig. 1 Fig1:**
[figure not shown]
An overview of the study

## Methods: participants, interventions, and outcomes

### Study setting {9}

The participants will be recruited, assessed, and subjected to intervention at Shandong Sport University, China.

### Eligibility criteria {10}

The inclusion and exclusion criteria are determined using the recommendations of the International Ankle Consortium [13].

#### Inclusion criteria

The initial sprain must have occurred at least 12 months prior to study enrollment, associated with inflammatory symptoms (pain and swelling), and created at least one interrupted day of the desired physical activity.They experienced at least two episodes of giving way in the 6 months prior to study enrollment.Their CAIT score must be ≤24.

#### Exclusion criteria

Positive anterior drawer test/Talar tilt testAlready a Tai Chi practitionerCurrently enrolled in an ankle rehabilitation programOther muscular, joint, or neurological conditions that affect the lower limb functionVisual, vestibular, and cognitive deficits

### Who will take informed consent? {26a}

After the patients are initially screened in accordance with the inclusion and exclusion criteria, eligible volunteers who agreed to participate will sign a written informed consent before the intervention. The informed consent process will be performed by the main researchers (HT) to explain the purpose, procedures, potential risks, benefits, and confidentiality of the information in detail.

### Additional consent provisions for collection and use of participant data and biological specimens {26b}

On the consent form, participants have the right to withdraw at any time and will be asked if they agree to the use of their data should they choose to withdraw from the trial. The participants will also be asked for permission for the research team to share relevant data with people from the universities taking part in the research or from regulatory authorities where relevant. This trial does not involve collecting biological specimens for storage.

## Interventions

### Explanation for the choice of comparators {6b}

FAI may be associated with the altered muscle activation ratio, impaired proprioception, and neuromuscular control. Several studies have found that Tai Chi, as a traditional Chinese exercise form, can improve ankle proprioception, static balance, lower extremity muscle strength, and neuromuscular reaction [11]. It has been widely used to treat patients with Parkinson’s disease, stroke, and knee osteoarthritis [14–16]. Tai Chi exercise may offer potential benefits to patients with FAI. However, the advantages for these patients who practice Tai Chi exercise as rehabilitation have not been rigorously tested. Therefore, the effects of Tai Chi exercise on neuromuscular function, joint biomechanics, and physical functioning in individuals with FAI should be further investigated to understand the clinical effects and relevant mechanism of the treatment. In this study, the participants in the STCEP group will receive a simplified Tai Chi. The STCEP emphasizes ankle joint movements and aims to promote the neuromuscular control of patients with FAI.

### Intervention description {11a}

#### STCEP group

This STCEP is derived from the traditional Yang style, and the core program consists of nine forms of STCEP (Fig. 2):

**Fig. 2 Fig2:**
[figure not shown]
The core program consisting of nine forms of STCEP

Form A: part the wild horse’s mane (stepping diagonally forward: left and right)

Form B: step back up and whirl arms (stepping backward: left and right)

Form C: brush knee and twist step (stepping forward: left and right)

Form D: cloud hands. Form E: single whip (stepping sideways: left and right)

Form F: pushing down and single on one leg (stepping diagonally forward: left and right)

Form G: heel kick (in situ: left and right)

Form H: grasp the bird’s tail (stepping sideways: left and right)

Form I: cross-hand (stepping sideways: left and right)

The exercise routine emphasizes the practice of ankle joint movements with more repetitions in multiple directions, which may help improve the neuromuscular function of ankle joints in patients with FAI. These movements are usually maintained in a semi-squat and one-leg stance, controlling the displacement of the center of gravity in three anatomical planes. The coordination of all body parts plays a vital role in maintaining precise motor control while keeping balance. Any simple action in the traditional 24-style Tai Chi program that involves fewer foot-ankle movements is removed. Afterward, the rest of the movements are rearranged according to the suggestions of Tai Chi experts. The exercise program will be specially designed to promote the neuromuscular control of patients with FAI.

The participants in the STCEP group will receive 12 weeks of the STCEP training, three sessions per week, and 60 min per session. Each session will include 5 min warm-up exercises, 50 min practice, and 5 min cool-down exercises. Every training session will be led and monitored by a professional Tai Chi instructor, who will carefully guide the exercise and correct inappropriate movements.

#### Control group

The participants in the control group will attend a low-intensity exercise program and receive health education but without similar training benefits in lower extremity weight bearing, strength, or balance [14]. The low-intensity exercise program will consist of whole body stretches, controlling breathing, and relaxation. Health education will cover health-related topics, such as ankle sprain, prevention, and rehabilitation. The weekly schedule will be identical to that of the STCEP group, and each session will include 40 min exercise and 20 min health education. Every training session will be led and monitored by a professional exercise instructor who will carefully guide the exercise and correct inappropriate movements.

### Criteria for discontinuing or modifying allocated interventions {11b}

Study patients will be allowed or asked to withdraw from the study if:
Participants decide to withdrawParticipants develop serious diseases, such as heart disease or strokeParticipants have an adverse reaction related to the STCEP programParticipants missed more than three training sessions in the 12-week program

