### Sample size {14}

The sample size is estimated on G* Power software (Germany) on the basis of a previous study [12], which reported that the CAIT score increased from 17.6 ± 2.1 cm to 28.4 ± 2.4 cm after 12 weeks of Tai Chi training. Under a significance level of 0.05, a statistical power of 0.80 in the two-tailed test, and a drop-out rate of 20% [24], the effect size and estimated required sample size of two groups are 0.57 [12] and 104, respectively.

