### Plans to promote participant retention and complete follow-up {18b}

Participants have the right to withdraw at any time and will be asked if they agree to the use of their data should they choose to withdraw from the trial. They will also be asked for permission for the research team to share relevant data with people from the universities taking part in the research or from regulatory authorities where relevant.

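### The protocol ties missed sessions and STCEP-related reactions to leaving the study, not just the training, so outcomes can be lost for reasons linked to adherence, harm and arm

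*Protocol article*

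**What the plan says.** All references are to the Protocol article.

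- **Criteria for discontinuing or modifying allocated interventions {11b}.** The heading concerns the intervention, but the operative sentence concerns the study: "Study patients will be allowed or asked to withdraw from the study if" one of four conditions is met. Two matter here. One is that the participant "missed more than three training sessions in the 12-week program". The other is an adverse reaction attributed to the STCEP programme; the control programme is not named.
- **Intervention description {11a}.** The Tai Chi arm receives "12 weeks of the STCEP training, three sessions per week, and 60 min per session". For the control arm, "The weekly schedule will be identical to that of the STCEP group".
- **Retention and complete follow-up {18b}.** Participants "will be asked if they agree to the use of their data should they choose to withdraw from the trial". This section does not mention continued assessment.
- **Adverse event reporting {22}.** A serious adverse event leads to stopping the intervention and to treatment; leaving the study is not mentioned. Adverse events are defined by reference to the intervention, without naming an arm. Ankle sprain and ankle pain are among the examples.
- **Non-adherence and missing data {20c}.** Withdrawals are to be handled by last observation carried forward (LOCF) and by multiple imputation.
- **Sample size {14}.** "Under a significance level of 0.05, a statistical power of 0.80 in the two-tailed test", with "a drop-out rate of 20"%, "the effect size and estimated required sample size of two groups are 0.57 [12] and 104, respectively".

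**The concern.** Stopping training and leaving the study are different events, and {11b} merges them. A participant who stops training can still attend the week 4, 8 and 12 assessments, and those outcomes are what an as-randomised comparison needs. A participant who is asked to leave the study has no stated route to those assessments.

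Both triggers are post-randomisation events. Poor attendance may be related to how the ankle is doing. An adverse reaction such as a sprain or ankle pain bears directly on the primary outcomes: the CAIT (which has a pain item), single-leg landing and the mSEBT. As worded, the adverse-reaction trigger can apply only in the Tai Chi arm, although the control arm also exercises. If Tai Chi participants whose ankles do badly leave and comparable control participants stay, the likely direction of error favours Tai Chi.

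LOCF and standard multiple imputation do not reliably recover outcomes whose absence depends on harm or non-adherence. The rule therefore creates missing data that the analysis must then try to repair.

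**Working it through.** **1. The threshold.** 12 weeks × 3 sessions = 36 sessions in each arm. Missing more than three means 4 or more, so a participant must attend at least 33 of 36 (33/36 = 91.7%) to stay clear of the rule.

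**2. The stated sample size.** Reading 0.57 as Cohen's d, a two-sided t test at 0.05 with power 0.80 needs 49.3, so 50 per arm or 100 in total, before drop-out. Allowing for 20% drop-out gives 100/0.80 = 125 (126 for equal arms). The stated 104 is not reproduced on these inputs. It is 4 above the no-drop-out figure, a margin of 4/104 = 3.8%. Taken at face value, the stated 20% allowance is 0.20 × 104 = 20.8, about 21 people.

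**3. How often the attendance rule would be triggered.** The article gives no expected attendance, so the absence rate per session, p, is an assumption shown as a range. Two models for X, the number of sessions missed:

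- independent absences: X ~ Binomial(36, p), and P(X ≥ 4) is the share triggered;
- absences that cluster by person: X ~ beta-binomial with mean p and a + b = 10.

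| Absence per session p | Mean sessions missed (36p) | Triggered, independent | Triggered, beta-binomial |
|---|---|---|---|
| 3% | 1.1 | 2% | 10% |
| 4% | 1.4 | 5% | 14% |
| 5% | 1.8 | 10% | 18% |
| 6.4% | 2.3 | 20% | 24% |
| 10% | 3.6 | 49% | 40% |

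The stated 20% allowance is reached at p = 6.4% with independent absences. With this amount of clustering it is reached at p = 5.5%.

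**4. Power on observed data.** Two-sided t test, d = 0.57, equal loss in both arms, 52 × (1 − loss) per arm:

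| Loss | Observed per arm | Power |
|---|---|---|
| 0% | 52 | 0.82 |
| 10% | 46.8 | 0.78 |
| 20% | 41.6 | 0.73 |
| 30% | 36.4 | 0.67 |

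These figures describe loss of information only. They do not measure bias, which depends on who leaves and cannot be computed from the article.

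**5. The sections side by side.** {11b}: an adverse reaction to STCEP leads to being allowed or asked to leave the study. {22}: a serious adverse event leads to stopping the intervention. The two differ on what ends (study or training) and on scope ({11b} names one arm, {22} names none). {18b} does not settle the matter, because it deals only with permission to use data.

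**The case against.** A reader might infer that anyone who misses a fourth session is removed automatically, that outcome collection then ends, and that what remains is a per-protocol comparison of highly adherent people, so that randomisation is broken. The article does not support that reading.

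- {11b} is permissive or a request, not an automatic removal, and no section says in terms that assessments stop.
- {20c} plans LOCF and multiple imputation for withdrawals, so these people are not simply dropped from the analysis.
- Many would leave partial data. With independent absences, the fourth miss falls after session 24 (the end of week 8 if sessions run to schedule) for about 68% of those triggered at 6.4% absence and about 56% at 10%. Imputation would have something to work with.

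A reader might also infer that the attendance rule by itself exhausts the 20% allowance. That is conditional. At 3% to 4% independent absence only 2% to 5% are triggered. {11c} plans contact three times a week, help with obstacles and teaching videos, which may keep attendance high.

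Finally, the definition of analysis sets is commonly left to a statistical analysis plan, so its absence here is not a fault.

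All of this stands, and it limits the claim. It does not remove it. Undefined discretion to ask non-adherent or harmed participants to leave adds a further route for selection. Partial data do not supply the week 12 outcome. The one-arm trigger and the mismatch between {11b} and {22} are present at any level of attendance.

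**Conclusion.** The concern holds in a limited form. As written, {11b} makes leaving the study a consequence of missed sessions or of an STCEP-related reaction, with no provision for later assessment and with a different consequence in {22}. If followed, it can produce informative missing outcomes that may differ by arm. The planned imputation softens this but cannot be relied on to correct it, so the randomised comparison is compromised rather than broken.

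The size is conditional on unstated attendance. The attendance rule alone would be triggered for about 2% of participants at 3% independent absence and 49% at 10%, or 10% to 40% over the same range with the clustering assumed above. It reaches the stated allowance at about 5.5% to 6.4% absence, roughly two missed sessions per person. A 20% loss would take power on observed data from 0.82 to about 0.73. These results assume that 0.57 is a standardised mean difference, that everyone who triggers the rule leaves, that loss is equal in the two arms, and the absence models stated. No estimate of bias is claimed.

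**What to change.** 1. In {11b}, separate stopping training from leaving the study. State that missed sessions, or stopping training, do not by themselves end study participation.
2. In {18b}, state that everyone randomised is invited to the week 4, 8 and 12 assessments unless they withdraw consent, and in the statistical section that they are analysed in the arm assigned.
3. Use the set with three or fewer missed sessions only for a sensitivity analysis. Attendance is already recorded under {11c}.
4. Reconcile {11b} and {22} on whether an adverse reaction ends the intervention or study participation, and on the arm or arms to which the criterion applies. That is for the investigators to decide; no clinical rule is proposed here.

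The cost is an amendment to the wording and some visits by non-adherent participants that are already on the schedule. The downside is that the as-randomised effect may be smaller than the effect in fully adherent participants. Outcomes not collected cannot be recovered later, so the change is worth most while participants are still in follow-up.

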### Strategies to improve adherence to interventions {11c}

The subjects’ attendance in every session will be recorded by the research assistant (who does not participate in follow-up evaluation and data analysis). The detailed exercise content and benefits will be informed to the participants to promote participant retention. The patients will be contacted and encouraged through WeChat three times a week. They will be asked about the factors that hinder their activities and solve them in time. In addition, teaching videos will be provided according to the teaching process to promote their exercise enthusiasm.

### Relevant concomitant care permitted or prohibited during the trial {11d}

During the trial, the participants will be informed to avoid taking part in any other regular rehabilitation training and maintain their previous lifestyle.

### Provisions for post-trial care {30}

Not applicable. There is no anticipated harm and compensation for trial participation.

### Outcomes {12}

Demographic information, primary outcomes, and secondary outcomes will be collected. Demographic information will be collected at baseline (1–2 weeks before randomization) via a questionnaire. Primary and secondary outcomes will be measured at baseline, 4th, 8th, and 12th weeks of training. The schedule of study outcome assessments is outlined in Fig. 3.

**Fig. 3 Fig3:**
[figure not shown]
The time schedule of enrolment, visits for participants, intervention, and assessments

#### Primary outcome assessments

Cumberland Ankle Instability ToolThe CAIT is a valid and reliable evaluative instrument used to assess self-rated ankle instability [17]. It consists of eight items for ankle instability in sports/daily activities and one item for ankle pain. The scores from the nine items are added to obtain a final score. The final score ranges from 0 (worst) to 30 (best).Biomechanical analysis during mSEBTmSEBT is a test that has been commonly utilized as a modified version of the SEBT to dynamic balance in clinics for the CAI groups [18]. In this test, participants stand on a single leg on the center of a force platform with hands on the waist as the starting position for the test. They maintain a single-leg stance and slowly reach the contralateral leg as far as they could along the anterior, posteromedial, or posterolateral directions. They tap their toes without shifting the body weight to the reaching limb and then return to the starting position while maintaining their single-leg stance balance for about 10 s. They perform three trials on each foot. In this study, the mean distance from the three trials will be used for analysis.Kinetic data will be simultaneously collected using two force plates (AMTI) with a sampling frequency of 1000 Hz in combination with the mEMG of the leg muscles for the mSEBT test. Rectangular electrodes with parallel bar electrodes are placed bilaterally over the muscle belly of the rectus femoris, biceps femoris, tibialis anterior, and peroneus longus [19].Biomechanical analysis during the single-leg drop landingA 40-cm-high box is placed 5 cm posterior to the force plate [20]. Before the test trial, the subjects are provided three trials to practice the maneuver. The participants are first asked to stand on the box with hands on the waist. The examiner gives the verbal command of “Ready,” and the participants stick out the tested leg and keep balance. As soon as hearing the command of “Start,” the participants jump straight down from the box, land on the tested leg at the center of the force plate, and stabilize as quickly as possible. They keep the single-leg stance balance for at least 5 s. Between trials, a 30-s rest will be provided. A trial will be discarded and repeated if the participants lose balance after landing or use their hands/feet are used to restore balance.Lower extremity kinematic data will be obtained using a three-dimensional motion capture system by 12 infrared cameras at 100 Hz (Vicon, Oxford, UK) and in combination with ground reaction force data, which will be measured by two force plates (AMTI) with a sampling frequency of 1000 Hz and in combination with the sEMG of the leg muscles for the landing task. The markers will be placed bilaterally on the first metatarsal head, first and fifth metatarsal phalangeal joints, medial and lateral malleoli, posterior calcaneus, medial and lateral femoral epicondyles, greater trochanters, anterior iliac spine, iliac crest, posterior iliac spine, and the fourth lumbar vertebra.
